## Introduction

### Background

Peru, similar to much of Latin America, has a concentrated HIV epidemic, where cisgender, sexual minority men (SMM; ie, gay, bisexual, and other men who have sex with men) are the primary population affected by HIV. While estimates vary across studies, most studies estimate 10% of HIV prevalence [1,2]; recent incidence estimates continue to be high, estimating an incidence rate of >6 cases per 100 person-years [3]. While there have been fewer studies focusing on sexually transmitted infections (STIs), existing studies point to a similar epidemic pattern [4,5]. Furthermore, epidemiological estimates indicate that between 32% and 39% of new HIV infections among adult cisgender SMM occur within primary partnerships (ie, among male couples) [6].

Although couples have been considered an important population for HIV prevention, no interventions focusing on couples have been tested or implemented in Peru. In this context, same-sex couples (eg, sexual and gender minorities) remain unacknowledged by Peruvian law and exist within a context of limited social and societal support [7]. In addition, while the health system provides both antiretroviral therapy (ART) and pre-exposure prophylaxis (PrEP), couples have not been integrated into considerations of treatment as prevention or PrEP provision, apart from pregnant women with a partner who is living with HIV. In short, HIV prevention care efforts in Peru have exclusively been limited to individual-level measures.

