#### Level 1: Individual Eligibility

Each individual participant within an adult cisgender SMM couple must meet the following individual-level eligibility criteria for the P3 pilot RCT: (1) currently identifies as male and was assigned male at birth (ie, cisgender); (2) be aged ≥18 years; (3) has access to a web-connected device (eg, smartphone, laptop, tablet, or computer); (4) lives in and plans to live in Lima, Peru, for the next 6 months; (5) reports being in a relationship with another cisgender, SMM partner and defines their partner as *someone they feel emotionally or romantically committed to above all others, such as a partner, husband, boyfriend, etc*.; (6) reports being in their relationship for a minimum of 3 months; (7) reports having had CAS with their relationship partner within the previous 3 months; (8) one of the relationship partners reports having had CAS with a casual sex partner in the same timeframe; (9) reports to having no history (ie, within prior 3 months and ever) of intimate partner violence; (10) reports not being coerced by their partner (or others) to participate in the study and related activities; (11) reports feeling safe in the current relationship to participate in the study and related activities; and (12) indicates willingness to test for HIV and other STIs at a local community–based organization at baseline and at 6 months after baseline.

Except for level 1 eligibility criterion number 8, individuals who do not meet all other above-mentioned criteria, will be deemed ineligible, thanked for their interest in the study, and provided a list of HIV and STI prevention resources and other health and relationship-oriented resources that are available in Lima, Peru. Individuals who meet all other criteria (other than number 8) will be prompted to complete an e-consent and enter complete contact information of themselves and their partner. Then, partner 2 will receive a study invite via WhatsApp, which will provide them with access to the eligibility screener and e-consent (if applicable). Level 2 eligibility criteria will automatically be evaluated once both partners complete the eligibility screener.

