#### Power, Sample Size, and Effect Size Estimations

All power calculations were performed with PASS 2020 [59]. For the couple-level analyses, with 60 couples randomized to 2 arms (30 couples in each), for outcome C, we will have 80% power to detect a difference of 0.75 SDs of the mean relationship functioning measure (large effect [60]) using a linear model. For the dichotomous outcomes A and B, we will have 80% power to detect an absolute difference of 35% between the intervention and delayed conditions using a chi-square test. Our power increases for the outcomes analyzed at the individual level, where the correlation between individuals within a dyad must be considered (ie, the interdependence of individuals nested within dyads). For the incidence rate of outcome D assuming Poisson distribution, 30 couples in each arm will have 80% power to detect a difference of 50% rate reduction in STI rate (including HIV) between the intervention and delayed conditions at 6 months assuming a within-pair coefficient of variation between clusters at 0.25 and the intraclass correlation coefficient as high as 0.1 (even higher ICCs do not reduce rate reduction measure in a significant or meaningful way magnitude wise). For all analyses, the α level was set at .05 with 95% CI. This is a feasibility and acceptability trial that is only powered to detect large effects; however, if effect sizes are lower than hypothesized, we will use that information to properly power a large-scale RCT.

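### The power section says within-couple ICCs above 0.1 barely affect outcome D; with two men per couple they cost power and raise the detectable reduction, and no figure or upper limit supports the remark

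*Protocol article*

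**What the plan says.** The statement is in the protocol article, Power, Sample Size, and Effect Size Estimations. The calculation is introduced with "For the incidence rate of outcome D assuming Poisson distribution". The target is "a difference of 50% rate reduction in STI rate (including HIV) between the intervention and delayed conditions at 6 months", with 30 couples per arm and 80% power, "assuming a within-pair coefficient of variation between clusters at 0.25 and the intraclass correlation coefficient as high as 0.1". A parenthesis follows: "even higher ICCs do not reduce rate reduction measure in a significant or meaningful way magnitude wise". The significance level is 0.05 throughout.

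The section gives no control-arm STI or HIV rate, no ICC above 0.1 and no result at a higher ICC. Shortly before, the same section says that correlation within a dyad has to be taken into account when individuals are analysed. It closes by saying that information from this pilot will be used to power a large-scale trial.

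**The concern.** The parenthesis is open-ended: it covers any ICC above 0.1. A couple is a cluster of two, so the variance inflation is 1 + ICC. That is 1.1 at ICC 0.1, 1.3 at 0.3 and 1.5 at 0.5, and the last two are not negligible beside the first. The remark presents the outcome D calculation as insensitive to within-couple correlation, which it is not.

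The larger consequence lies in the next trial. If its designers take from this section that values above 0.1 can be ignored, and the true ICC is higher, that trial will be too small. Some linkage of infections within couples is plausible, since each man qualifies only if he "reports having had CAS with their relationship partner within the previous 3 months". The documents give no value for the ICC.

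**Working it through.** **Inputs from the documents.** 30 couples per arm, two men per couple (60 men per arm), 1:1 allocation, rate ratio 0.5, Poisson counts over 6 months, alpha 0.05, 80% power at ICC 0.1.

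**Assumptions.** A two-sided test, because the power section does not give sidedness. ICCs of 0.2 to 1, taken as a range because the documents name none above 0.1.

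**1. The stated 80%.** It cannot be reproduced, because no control rate is given. It can only be used as an anchor. The control mean per man over 6 months, m, that would give 80% on the rate-difference scale solves

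m × 0.5 = (1.960 + 0.842) × √[1.5 m × 1.1 / 60]

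so m = 7.849 × 1.5 × 1.1 / (60 × 0.25) = 0.863 infections per man in 6 months, or about 1.73 per man-year. On the log rate-ratio scale the same step gives 1.80.

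**2. Power for a 50% reduction when only the ICC changes.** The standard error grows with √(1 + ICC), so

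power = Φ(2.802 × √[1.1 / (1 + ICC)] − 1.960).

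The control rate cancels in this expression once the 80% anchor is accepted. At ICC 0.3, for example, 2.802 × √(1.1/1.3) − 1.960 = 0.617, and Φ(0.617) = 73.1%.

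**3. Reduction detectable with 80% power.** Keep m = 0.863 and solve for the rate ratio q in

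m(1 − q) = 2.802 × √[m(1 + q)(1 + ICC) / 60].

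**4. Couples per arm for 80% power at a 50% reduction.** 30 × (1 + ICC) / 1.1, rounded up.

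| ICC | Power for 50% reduction | Detectable reduction | Couples per arm |
|---|---|---|---|
| 0.1 | 80% (anchor) | 50% | 30 |
| 0.2 | 76.5% | 51.9% | 33 |
| 0.3 | 73.1% | 53.7% | 36 (35.5) |
| 0.5 | 67.0% | 57.0% | 41 (40.9) |
| 0.7 | 61.5% | 60.0% | 47 (46.4) |
| 1 | 54.7% | 64.2% | 55 (54.5) |

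**5. Robustness of the check.** On the log scale, power is the same and the detectable reductions are 53.9%, 57.5% and 60.9% at ICC 0.3, 0.5 and 0.7. If the coefficient of variation of 0.25 is kept as a separate variance term and the anchor is solved again, power is 73.6–73.7% at ICC 0.3 and 67.8–67.9% at 0.5. Simulating correlated Poisson pairs at the anchored rate (20,000 trials, couple-level t test) gives 79%, 73%, 66% and 61% at ICC 0.1, 0.3, 0.5 and 0.7.

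**The case against.** **The sentence is about the rate reduction, not power.** This is the best defence. Read literally, the parenthesis concerns the size of the detectable reduction. On that scale the shift is more modest: about 4 points at ICC 0.3 and 7 at 0.5. In a pilot said to be powered only for large effects, whether 4 points is meaningful is a matter of judgement. This stands as far as it goes. A reader might infer that the protocol promises 80% power for a 50% reduction at any ICC, but it does not say so. Still, the remark has no upper limit, and by ICC 0.7 the detectable reduction is 60%.

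**The anchor is weak.** This also stands. A control rate of about 1.7 infections per man-year appears nowhere in the document. With assumed rates of 0.06, 0.3 and 0.8 per man-year, power at ICC 0.1 would be about 7%, 21% and 46–48%, and the ICC would then be a secondary matter. The power series above should therefore not be printed as established.

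**The population does not prove a high ICC.** A reader might infer one from the statement that "between 32% and 39% of new HIV infections among adult cisgender SMM occur within primary partnerships". That figure describes where infections arise and is not a correlation of combined STI and HIV counts. Also, 20 of the 30 planned couples per arm are serodiscordant or seroconcordant positive, so both partners cannot newly acquire HIV.

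**The coefficient of variation is not a second error.** Values above 0.25 would also reduce power, but the protocol makes no claim of robustness to them. Under a Poisson model the two inputs are linked: at the anchored rate, an ICC of 0.3 or 0.5 corresponds to a coefficient of variation of about 0.7 or 1.05.

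**More couples were enrolled.** The Results report 74. Assuming 37 per arm, multiplying by √(37/30) inside Φ gives about 82% at ICC 0.3 and 76% at 0.5. This softens the loss for the trial as run, but power still falls as the ICC rises.

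**The primary test differs.** Primary Analyses compares proportions of couples by chi-square, whereas the check follows the Poisson rate model of the power statement, which is the claim at issue.

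**Conclusion.** The parenthesis claims a robustness that a two-person cluster design does not have. Conditional on the stated 80% at ICC 0.1, moving to ICC 0.3, 0.5 or 0.7 costs about 7, 13 or 18 points of power for a 50% reduction. Equivalently, it takes 6, 11 or 17 more couples per arm to hold 80%. On the scale the sentence names, the loss is smaller but not nil.

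The result rests on a two-sided 0.05 test, a design effect of 1 + ICC and an 80% anchor that cannot be verified. The documents do not show that the true ICC exceeds 0.1 or that the 80% itself is wrong. Nor do they say that 0.1 will be carried into the next trial; that is a risk the wording creates. The conduct and analysis of the pilot are unaffected, so this is a correction to a stated property of the design.

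**What to change.** - Delete the parenthesis about higher ICCs.
- State the control-arm STI/HIV rate used in the outcome D calculation.
- At that rate, give both power for a 50% reduction and the reduction detectable with 80% power over a range of ICCs, for example 0.1, 0.3, 0.5 and 0.7. Compute these from the actual rate; do not copy the anchored series above.
- Report the pilot's within-couple ICC for STI/HIV infection with its confidence interval. Use that interval, not 0.1 alone, when sizing the efficacy trial. The estimate will be imprecise with this many couples, which is why the interval matters more than the point value.

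The cost is a restated sentence or two and one descriptive estimate from data already collected. No extra enrolment is needed. The price is a less favourable stated sensitivity for outcome D.

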#### Missing Data

Reminders and incentives will be used to maximize participation in the follow-ups. For the primary outcome measures, any missing data due to attrition would be handled as mentioned in the Intention to Treat section. In addition, missing data mechanisms [61-63] will be examined by comparing differences between the dropouts and the observed data. We will perform 25 conditional model-based multiple imputations within group using SAS PROC MI, and will aggregate the results into an overall group, time, and group-by-time interaction with SAS PROC MIANALYZE to provide unbiased intervention effects and their variances. This will also be advantageous if there is a differential dropout for the delayed condition due to wait time. To ensure the validity of the imputed data, 4 parallel models will be performed as a sensitivity analysis on (1) imputed data, (2) completers-only data, (3) assuming adverse outcome for those missing, and (4) applying GLMMs that have the advantage of handling incomplete unbalanced repeated-measures data by incorporating population average and subject-level trajectories, and in turn providing unbiased estimates of parameter of interests. If necessary, post hoc power analyses will be performed using the bootstrap method to calculate the observed power for the detected effect size.

#### Exploratory Secondary Analysis: APIM

To analyze for actor-partner effects using the APIM framework, we will arrange the data in a pairwise format following recommendations provided by Kenny et al [17]. Actor and partner effects will then be estimated using the generalized estimated equations algorithm described by Loeys et al [64], which accounts for the correlation between individuals within a couple using a robust variance estimate. The Wald test based on robust variance of the generalized estimated equations models performs quite well in testing actor and partner effects when the number of dyads is >50 [65]. Several models will be examined for significant actor-partner effects about cisgender SMM couples’ outcomes of A and B. For each outcome, 2 actor-partner models will be constructed to test the impact of demographics and common relationship characteristics (model 1) separately from the impact of the average absolute change in relationship functioning variables (eg, couple mean and within-dyad difference) over time (model 2). Trial arm assignment will be controlled in each actor-partner model as a potential confounder. The parameter estimates produced from these models will be used to detect the actor-partner effects. To make the interpretation of the actor-partner effects more intuitive, we will convert the coefficients and 95% confidence limits to adjusted relative risk ratio and corresponding 95% confidence limits for presentation. Two-sided *P* values <.05 will be considered statistically significant. We will also consider analyzing joint and mutual joint effects based on time availability.

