#### Aim 3: Preliminary Efficacy of the Intervention

Using the 6-month pilot RCT, this research will examine the preliminary efficacy of the intervention on couples: (A) formation and adherence to an HIV and STI prevention care plan containing evidence-based strategies (eg, ART for U=U, PrEP, and routine testing); (B) formation and adherence to a detailed sexual agreement, (C) relationship functioning (eg, mutual constructive communication and self-efficacy of decision-making and working together), and (D) self-reported and biomarker-confirmed indicators of vulnerability vis-à-vis sexual behaviors (eg, CAS) and HIV and STIs. The pilot RCT will have an allocation ratio of 1:1 and block randomization with a block size of 2, with blocks defined by dyad serostatus. Outcomes A and B will be dichotomous, outcome C will be continuous based on a bounded Likert scales, whereas outcome D will be a count variable based on STI incidence, HIV incidence, and CAS.

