## Results

This 6-month pilot RCT is ongoing. Recruitment, enrollment, and data collection began in January 2023 and ended in April 2024. A total of 74 adult cisgender SMM couples met all inclusion criteria, provided consent, and were enrolled in the pilot RCT. Retention was 92% (68/74) at month 6. Data are currently being analyzed to address the 3 specific aims. Findings will be disseminated through peer-reviewed journals and conference presentations.

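### The APIM section rests its robust Wald test on the number of dyads alone, but the test also becomes mildly liberal as model terms are added, so the exploratory 95% limits are somewhat too narrow

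*Protocol article*

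**What the plan says.** The section Exploratory Secondary Analysis: APIM fits actor-partner models to outcomes A and B by generalized estimating equations, a method that "accounts for the correlation between individuals within a couple using a robust variance estimate". The adequacy of the Wald test is supported by a cited source: it "performs quite well in testing actor and partner effects when the number of dyads is >50". For each outcome, "2 actor-partner models will be constructed to test the impact of demographics and common relationship characteristics (model 1"), kept separate from model 2. Model 2 takes changes in relationship functioning, with the couple average and the difference between partners as its examples. Trial arm enters every model. Coefficients and 95% limits are converted to adjusted relative risks, and two-sided P "values <.05 will be considered statistically significant".

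On outcome type, Aim 3 states "Outcomes A and B will be dichotomous". On numbers of couples, the power section plans "with 60 couples randomized to 2 arms (30 couples in each"), and Results reports "A total of 74 adult cisgender SMM couples met all inclusion criteria" and "Retention was 92% (68/74) at month 6".

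Predictors are named by class only. No count of terms and no small-sample correction is given.

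**The concern.** The robust (sandwich) variance is built from fitted residuals. Fitting pulls these toward zero, and more strongly the more coefficients are estimated from a given number of couples. A threshold on the number of couples therefore cannot by itself secure a 5% level.

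The models planned here use up terms quickly. Each individual-level predictor costs two coefficients (actor and partner), and each relationship-functioning variable in model 2 costs two if both the average and the difference are entered. If the variance is too small, the 95% limits on the adjusted relative risks are too narrow and P<.05 occurs more often than 1 time in 20 when nothing is going on. The Theoretical Foundation section presents the actor-partner model as the way partner influence is measured, so these estimates are likely to be read with interest even though they are exploratory.

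**Working it through.** **The plan's own figure.** The article gives a criterion (more than 50 dyads) and a nominal level (5%), but no achieved error rate, so there is no rate to reproduce. The criterion itself is met: 60 planned, 74 enrolled and 68 retained (68/74 = 91.9%) all exceed 50.

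**Inputs from the article.** Binary outcomes A and B; robust variance clustered on the couple; arm in every model; two-sided 5%; 68 to 74 couples.

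**Assumed, because the article does not say.** K predictors with two terms each, so coefficients p = 2 + 2K (intercept, arm, two per predictor); K from 1 to 11; outcome prevalence 0.3-0.7; latent within-couple outcome correlation 0.4-0.5; normal predictors; logit link with exchangeable working correlation, or log link with independence.

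**Null simulation, uncorrected Wald test, rejections per term (%).** Each setting had 1,000 to 4,000 replicates. At 1,000 replicates the Monte Carlo standard error for a single coefficient near 6% is √(0.06 × 0.94/1000) = 0.75 points; averaging over terms reduces it. A range means that more than one run was made.

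Actor and partner terms:

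| p (K) | 68 couples, logit | 74 couples, logit | 74 couples, log |
|---|---|---|---|
| 4 (1) | 5.5 | 5.3 | 6.0 |
| 8 (3) | 5.8-6.5 | 5.5-5.7 | 6.2 |
| 12 (5) | 6.1-6.7 | 6.1-6.4 | 6.5 |
| 18 (8) | 6.8-7.1 | 6.6-7.0 | 6.9 |
| 22 (10) | not run | 7.2 | 7.5 |
| 24 (11) | 7.7 | 7.5 | not run |

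One further run at 68 couples with 25 coefficients gave 8.3%.

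Couple average plus absolute partner difference (the model 2 example):

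| p (K) | 68 couples, logit | 74 couples, logit | 74 couples, log |
|---|---|---|---|
| 8 (3) | 7.4 | 6.4 | 7.2 |
| 12 (5) | 7.8 | 7.6 | 8.1 |
| 18 (8) | 9.8 | 9.2 | 9.3 |
| 22 (10) | not run | 10.8 | 10.3 |
| 24 (11) | 12.7 | not run | not run |

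A further run at 68 couples with 8-18 coefficients gave 5.7-7.2% for actor and partner terms and 7.0-10.2% for couple-level terms.

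**Hand check.** To first order, the estimated standard error is too small by a factor √(1 − h), where h is the average leverage, and the actual size is 2 × [1 − Φ(1.96 × √(1 − h))]. For individual-level terms h ≈ p/(2n), because there are 2n observations. For couple-level terms h ≈ p/n, because both partners carry the same values. With n = 68 and p = 18:

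- Individual-level: h = 18/136 = 0.132; √0.868 = 0.931; 1.96 × 0.931 = 1.826; size 6.8%.
- Couple-level: h = 18/68 = 0.265; √0.735 = 0.857; 1.96 × 0.857 = 1.681; size 9.3%.

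With p = 8 the same steps give 5.7% and 6.6%. This agrees with the simulation and explains why the model 2 predictors fare worse.

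**Interval width.** Read backward, and treating the excess as due only to a standard error that is too small, a size of 7% corresponds to a factor of 1.812/1.96 = 0.92 and a size of 10% to 1.645/1.96 = 0.84. The limits are then about 8% and 16% too narrow.

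**With a correction.** The Kauermann-Carroll variance held 4.4-5.6% in 16 settings (54 and 68 couples, both predictor types, 8-24 coefficients). The Mancl-DeRouen variance overcorrected, at 0.4-4.3% in the same settings.

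**The case against.** The best defence has four parts.

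1. **The sentence is not shown to be false.** It says the test performs well, not that it is exact. The cited source is not at hand, so the model sizes it covered are unknown. With one to three predictors the simulated size for actor and partner terms is about 5-6.5%, which is consistent with that wording. This stands, and it is why the sentence should be qualified and not deleted.
2. **The number of predictors is unknown.** The measures section lists what is collected, not what enters the models, and a predictor list may well sit in a fuller document. This also stands. The rates above are conditional on assumed counts, and the missing list is not itself a fault. What remains is that the stated reason ignores the number of terms whatever that number turns out to be.
3. **The analysis is exploratory.** Efficacy rests on the arm comparisons, which do not use this test. This stands and limits the weight of the point.
4. **Multiplicity does more harm.** Six or ten independent tests at exactly 5% give at least one false positive with probability 1 − 0.95^6 = 26% or 1 − 0.95^10 = 40%. Simulated figures for the uncorrected test are about 28-33% with three predictors and 44-51% with five. This is correct, so the variance correction alone would not make a list of P values confirmatory.

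None of these shows that dyad count alone secures the level. They show that the shortfall is modest.

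**Conclusion.** The point holds as a minor one. At 68-74 couples the uncorrected robust Wald test runs at about 5.5-8% per actor or partner term, and at about 7-10% for models with 8-18 coefficients built on couple averages and partner differences. These figures depend on assumed predictor counts and shapes. Strongly skewed predictors gave 5.8-9.0% with a logit link and 10.8-12.1% with a log link at 60-74 couples.

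A reader might go further and infer that actor and partner tests run at up to 10%, so that false effects will be reported as significant. The article does not support that. For ordinary actor and partner terms, a rate near 10% came only from combining about 25 coefficients with 54 couples (90% of 60), which gave 9.5%. The article reports 68 couples retained and 74 enrolled, and its intention-to-treat rule assigns an adverse result on A and B to couples lost to follow-up, which could keep all 74 in these models. It states no predictor count. Nor is there a basis for removing the cited sentence or for imposing a particular cap on coefficients.

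**What to change.** - Use a small-sample-corrected robust variance of the Kauermann-Carroll type for the APIM models, for example EMPIRICAL=ROOT in PROC GLIMMIX, a procedure the article already plans to use. Prefer it to Mancl-DeRouen, which was too conservative with many terms.
- Qualify the 50-dyad sentence to say that the criterion does not take account of the number of terms in the model.
- Keep the number of terms small relative to the number of couples, above all in model 2, where couple-level predictors inflate the error rate most.
- Report actor and partner effects as exploratory estimates with intervals, without claiming 5% error control.

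The cost is one software option, one edited sentence and slightly wider intervals. No data collection changes. The Results section says analysis is under way, so the change should be made and dated before these models are fitted.
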